## Methods/design

The project will apply a step-wise study design with three study phases in two level one perinatal maternity clinics: *Implementation phase and pre-experimental study* (Phase 1), a *quasi-experimental efficacy study* (Phase 2), and a *case control study* (Phase 3; Fig. 2).

**Fig. 2 Fig2:**
[figure not shown]
Study flow with project phases and stages, study participants and outcome (Study Flowcharts for all three Phases are in the Appendix). *Note.* The phases consist of different stages (see Table 3). Stages A to C (see Table 3) will be addressed in Phase 1. Stages D and E will be addressed in Phase 1 and 3

For the study flow of enrollment and interventions for each phase, see the Appendix. All study participants are professionals, patients and social support providers in two participating gynecology and obstetrics clinics, therefore, they receive the regular treatment as patients in terms of healthcare or as staff with human resource (HR) management. Table 2 provides a summary of outcome variables across the study phases.

**Table 2 Tab2:** Overview over the outcome variables and covariates considered in the different study phases

	Phase 1		Phase 2		Phase 3	
	T1	T2	T1	T2	T1	T2
Primary outcomes						
Communication competences^1^	X	X	X	X	X	X
Preventable adverse events (pAEs)^2^	X	X	X	X	X	X
Secondary outcomes						
Healthcare provider satisfaction^3^	X	X	X	X	X	X
Patient/treatment satisfaction^3^ (patients/social support providers)			X	X	X	X
Training-related outcomes^4^	X	X	X	X	X	X
Personal outcomes^5^	X	X	X	X	X	X
Organizational outcomes						
Adherence safety culture^6^	X	X	X	X	X	X
Subjective safety culture^7^			X	X	X	X
Covariates						
Socio-demographic variables including migration status^8^	X		X		X	

*Note:* Examples for the measurements are:

^1^ Self-developed questionnaire

^2^ Operationalized via trigger events (such as unavailable staff, equipment failure, readmissions, length of stay, communication error) as defined by [54, 55]

^3^ Nurses’ job satisfaction scale [56]

^4^ HAPA questionnaire including outcome expectancies, goals and intentions/motivation, action planning and coping planning, behavior, self-efficacy, perceived stress see [25, 42, 45–48]

^5^ Emotional exhaustion, depersonalization, perceived social support [4, 57]

^6^ The Hygiene Inventory - 23 items (HI-23) [58]

^7^ Measures equivalent to the ones used in [59, 60]

^8^ Age, gender, education, professional experience, depressive symptoms, anxiety and migration [61, 62]

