**Methods:**

The study will take place in two maternity clinics in Germany. In line with previous studies of complex interventions, it is divided into three interdependent phases. Each phase provides its own methods and data. Phase 1: Needs assessment and a training for staff (*n* = 140) tested in a pre-experimental study with a pre/post-design. Phase 2: Assessment of communication training for patients and their social support providers (*n* = 423) in a randomized controlled study. Phase 3: Assessment of an app supporting the communication between staff, patients, and their social support providers (*n* = 423) in a case-control study. The primary outcome is improvement of communication competencies. A range of other implementation outcomes will also be assessed (i.e. pAEs, patient/treatment satisfaction, work satisfaction, safety culture, training-related outcomes).

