With regard to the prevalence of pAEs, an observation study conducted in obstetrics and gynecology by November et al. in Boston, USA, identified forty-one pAEs within a time frame of 12-weeks [14]. In a recent international meta-analysis by Tanaka, Eriksson and Obermair, the incidence of adverse events in gynecological hospital admissions was 10.8% [15]. Of these adverse events, 52.5% could have been prevented and 1.2% resulted in death. The authors note that “preventability can only be assessed from available documentation and can be influenced by study personnel experience, and knowledge [ …] amendments [ …] need to take place to improve healthcare delivery in gynecology” (p. 198f). Improved communication is also likely to result in better healthcare provider and patient outcomes. For instance, a recent study has discussed the importance of communication between healthcare professionals and physician well-being. Physician burnout was associated with an increased risk for unsafe care, unprofessional behaviors, and low patient satisfaction [16–18]. This is especially true when under time constraints [6, 19, 20].

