Patient satisfaction is an important patient-centric outcome for a gynecological clinic and its staff. Giving birth can be a positive experience but it can also be painful. The more pain a mother experiences and the longer her convalescence lasts, the more it affects her satisfaction. Despite healthcare providers’ awareness of this relationship, there is still room for improvement in pain treatment during labor [21]. Effective communication is one key in pain management, especially under high stress and demands. Accordingly, this needs to be improved based on empirical evidence. Empirical evidence on the effectiveness of communication training is ambiguous. Several studies show that communication errors and barriers can be reduced by efficient training programs that help individuals to identify, prevent or manage such errors and barriers. For instance, one study demonstrated that a standardized team-training program for healthcare professionals in obstetric units, based on an analysis of common causes for adverse events, was found to successfully raise professionals’ confidence in dealing with complex emergency situations [12]. Perceived ownership of staff has been demonstrated to be the key moderator of the effectiveness of such trainings [22]. However, a recent systematic review concluded that “Current evidence is inadequate to inform content of training or practice“[9]. Thus, communication *between professionals and with patients* should be structured [23, 24] specifically to the specific context. The primary aim of our project, which is theoretically grounded in models of health-related communication [11] and behavioral change (HAPA) [25], is to improve communication behaviors in gynecology and obstetrics. The second aim is to reduce pAEs and increase healthcare provider and patient satisfaction.

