Expectant mother or *patient* in gynecology and obstetrics or *social support providers* (spouse/partner, relative, close friend) to be recipient of the training *Professional* in a gynecology and obstetrics hospital to be trainer of the patients and the social support providers	Not proficient in the German language and/or does not have the capability of writing Severe cognitive deficits (unable to read/write/answer questions) and impairments due to diagnosed brain injuries, neurological disorders, etc. Insufficient corrected eyesight (patients must be able to read on the cell phone) Participation in another research study or intervention trial conducted in the clinic
Aged 18 years and above	Younger than 18 years
Healthy volunteers	High risk, emergency case
Declaration of consent for participation in the study	Withdraw of consent for participation in the study at any point in time

According to a power analysis, a sample of *N* = 352 is necessary (alpha error = 0.05, power = 80%, to be analyzed IG _analysis_: *N* = 176; CG _analysis_: *N* = 176) in order to detect an effect size of *d* = 0.3. With an assumed drop-out rate of 20%, *N* = 423 participants (IG _recruited_: *N* = 212; CG _recruited_: *N* = 211) have to be recruited in the study. The pAEs will be collected on an individual basis (anonymized) and coded according to the communication competences (see Fig. 5 in Appendix).

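### The abstract names communication competencies as the only primary outcome, but Table 2 also lists pAEs as primary, and the sole power analysis gives no pAE rate or target reduction

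*Protocol article*

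**What the plan says.** The article describes the standing of pAEs in several places.

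- **Abstract, Methods:** "The primary outcome is improvement of communication competencies". The next sentence reads "A range of other implementation outcomes will also be assessed (i.e. pAEs, patient/treatment satisfaction, work satisfaction, safety culture, training-related outcomes", so pAEs are outside the primary outcome.
- **Background:** improving communication behaviour is the primary aim, and "The second aim is to reduce pAEs and increase healthcare provider and patient satisfaction".
- **Research questions and hypotheses:** communication, satisfaction and pAEs are grouped together as main outcomes. Hypotheses 3, 6 and 9 each predict a significant fall in the number and severity of pAEs.
- **Table 2:** communication competences and "Preventable adverse events (pAEs)^2" are the two rows under the primary heading, marked for all three phases. Satisfaction and training-related outcomes come under the secondary heading.

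The Phase 1, 2 and 3 sections refer to Table 2, in places together with Table 1, for the target criteria. The Phase 2 analysis section applies superiority tests to those criteria.

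The one power analysis is in the Phase 2 Procedure section: "According to a power analysis, a sample of *N* = 352 is necessary", with "alpha error = 0.05, power = 80"%, "in order to detect an effect size of *d* = 0.3". It names no outcome.

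**The concern.** The abstract and Table 2 cannot both be right about the primary outcome, and no detail left to another document can make both true. If the label is still open when results arrive, either outcome can be presented as the one on which the trial was to be judged.

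The second consequence concerns power. Someone who reads Table 2 next to the sample size paragraph could take the stated 80% to apply to both primary rows. The calculation is for a standardised mean difference, which suits a questionnaire score. Nothing in it deals with how often pAEs occur or how far they are expected to fall.

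**Working it through.** **1. Reproduce the plan's figure.** Inputs from the Phase 2 Procedure section: d = 0.3, alpha 0.05, power 80%, equal arms. Sidedness is not stated.

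- Normal approximation, two-sided: n = 2(1.960 + 0.842)²/0.3² = 174.4, so 175 per arm.
- Two-sample t-test, two-sided: 175.4, so 176 per arm and 352 in total. This matches the plan.
- One-sided: about 138 per arm, which does not match.

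The plan's figure is thus a two-sided comparison of means on a continuous score.

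**2. Look for pAE inputs.** The article gives no planning rate and no target reduction. The only per-admission incidence is background literature: "the incidence of adverse events in gynecological hospital admissions was 10.8"%, of which 52.5% were preventable. This gives 0.108 × 0.525 = 0.0567, or 0.0567 × 176 ≈ 10 expected events in the control arm.

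**3. Illustrate power for a yes/no pAE outcome per woman.** Assumptions: independent women, 176 per arm, Pearson chi-square, two-sided 0.05. For event counts a and b, with p̄ = (a + b)/(2n), reject if (a/n − b/n)² / [p̄(1 − p̄)·2/n] ≥ 3.84. Power is the sum of Bin(a; n, p₁)·Bin(b; n, p₂) over all rejecting pairs, with p₂ = p₁(1 − reduction).

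| Control rate | Basis | 25% reduction | 30% | 50% | 75% |
|---|---|---|---|---|---|
| 5.67% | background, preventable | 9% | 11% | 26% | 60% |
| 10.8% | background, all adverse events | 14% | 18% | 46% | 88% |
| 25% | assumed, to show sensitivity | 29% | 41% | 86% | >99% |

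Every reduction in the table is an assumption, since the article states none. The normal approximation gives 58% instead of 60% for a 75% reduction at 5.67%, and otherwise agrees closely there. At 5.67%, 80% power needs a reduction of roughly 87% by enumeration and 91% by the approximation used as a cross-check. A halving reaches 80% power only at a control rate of about 22%.

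**4. Who is counted.** The 423 participants can include social support providers, whereas pAEs concern women and newborns. If half of each arm were supporters (88 women per arm, an illustration), power for a halving falls to 13% at a 5.67% rate and 57% at a 25% rate.

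**The case against.** It can be argued that the abstract and the Background agree on the order, that Table 2's heading is the outlier, and that the article never claims power for pAEs. That is fair, and it makes the repair easy. It does not remove the contradiction, because Table 2 is where the analysis sections send the reader.

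The argument is stronger on the size of the power problem, and most of it stands.

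- A reader might infer that the trial has roughly 25% power for pAEs on the article's own figures. It does not follow: that value needs a 50% reduction, which appears nowhere.
- The 5.67% comes from gynecological admissions in the literature. The trial counts broader trigger events, including staff availability, equipment problems and communication errors, so its rate could be much higher. Phase 1 Stage A is to measure prevalence.
- The hypotheses concern number and severity, and the planned analysis uses mixed models. A count analysis could have different power from a comparison of two proportions.
- Excluding high-risk and emergency cases (Table 6) need not lower the rate of such trigger events.

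A reader might also infer a multiplicity fault, with familywise error up to 1 − 0.95² = 9.75%. That requires independent tests and a rule that either outcome alone suffices. The article states no such rule. If both outcomes had to succeed, no split of alpha would be needed, and multiplicity may be handled in the full protocol or the SAP, which are not shown.

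**Conclusion.** The point holds as an internal contradiction: the abstract and the stated aims make communication competences primary and pAEs subordinate, while Table 2 makes both primary. This needs no assumption about rates, and it has to be settled because it decides what counts as success.

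It also holds that the 80% power cannot be taken to cover pAEs, because the calculation reproduces for a continuous score and contains no pAE input. How far short the trial falls is not determined by the article. For a binary outcome at 176 per arm, the illustration runs from 9% to 60% at a 5.67% rate (reductions of 25% to 75%), and a halving has 46% power at 10.8% and 86% at an assumed 25%. Each figure would be lower if some of the 176 are supporters, and the trigger-event definition or a count analysis could change them. It would go too far to say that the trial could not show an effect on pAEs.

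**What to change.** Before outcome data are seen, bring Table 2 into line with the abstract and the Background:

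- Keep communication competences as the sole primary outcome, and say that alpha 0.05 and N = 352 apply to it in Phase 2.
- List pAEs as secondary, reported per woman as an estimate with a 95% confidence interval, and state that the sample size was not calculated for them.
- Label hypotheses 3, 6 and 9 as secondary so that they match.

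If the sponsor instead wants pAEs as a co-primary outcome, the abstract must say so. The plan should then give the testing rule (either outcome or both), the assumed pAE rate and reduction, and the power that results.

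The first route costs a table edit, a sentence on the sample size and the relabelling of three hypotheses. Its downside is that pAEs lose the primary label, which the abstract already withholds. The second route needs a further power calculation and may show that the planned numbers are too small for pAEs.

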### Phase 1: implementation phase and pre-experimental study

#### Overview of research questions and methods

For Phase 1, we conduct a needs assessment with regard to overall patient safety, based on the approach proposed by van Sluisveld et al., which aimed to improve the safety of patient transfers in intensive care units [63]. In the current project, this approach will be applied to gynecology and obstetrics clinics with their staff, patients (expecting mothers/women who are about to deliver or who gave birth recently), and social support providers (e.g., spouse/partner, relatives, close friends¸ Fig. 2). The approach differentiates into stages A to E (see Table 3), which will be conducted accordingly in the current study.

**Table 3 Tab3:** Implementation phase: Research questions, methods, study participants and target criteria with regards to patient safety

Stage	Research questions	Methods	Target group/data source	Outcome measures
A	What is the status of communication competences?	Questionnaire (self-developed)	Healthcare providers	Communication competences as described by the SACCIA framework
	What is the prevalence of pAEs?	Routine data Mixed Methods study, Analysis of birth protocols (observations), staff questionnaire	Anonymous routine data of the hospital from the last year (2018), birth protocols and patient records, subjective prevalence	Quality indicators: pAEs such as unavailable staff, equipment failure, readmissions, length of stay, communication errors
B	What are effective interventions to improve safety and communication in everyday hospital life?	Scoping review	Pubmed, PsychInfo, Cochrane Database Web of Science Core Collection database^1^	Overview of effective interventions and effect sizes
C	What is the adherence for current patient safety measures (e.g., hand hygiene)?	Questionnaire, e.g., HI-23	All professionals at both intervention sites	Adherence to patient safety measures; relationships between adherence and quality indicators incl. patients’ satisfaction with their treatment and professionals work satisfaction
D	What are the resources and barriers for the implementation of an intervention in order to optimize communication in everyday hospital life?	Ethnographic observation; Individual semi-structured and focus group interviews	Physicians, nursing staff, training assistants, psychologists, midwives	Resources and barriers classified according to: (1.) intervention characteristics; (2.) societal context, (3.) implementation characteristics, (4.) institutional characteristics, (5.) social context, (6.) professional characteristics, and (7.) patient characteristics.
E	What is an appropriate strategy to implement effective interventions to optimize communication?	Intervention mapping with the method of Bartholomew and Kok (2011), triangulation of results from previous stages	Matching of data from interviews, focus groups and questionnaires with evidence from the literature	Implementation strategy tailored to the found resources and barriers to the implementation of effective interventions to increase patient safety

*Note:* pAEs = preventable adverse events; the content of this table is based on Table 2 in [63]

^1^The literature search for this paper used the following search term combinations:

Communication Training/Intervention AND Resource AND Implementation AND Health Experts

Communication Training/Intervention AND Barrier AND Implementation AND Professionals/Patients

Communication Training/Intervention AND Resource/Barrier AND Outcome Expectancies

We always maintained “Communication, Training, Intervention, Resource, Barrier” as search terms and will refine the larger searches with the following terms: Intention, plan, behavior, social-cognitive

Observations for the ethnographic analyses will be recorded using a standardized observation protocol [30]. The qualitative data will be analyzed in terms of inductive content analysis and will be used to develop the training. The details of this approach are described in Sluisveld et al. (2013) [63]. Focus groups and interviews will be conducted with partially standardized guidelines with at least one person from each occupational group in order to gain an impression of potential resources and barriers as comprehensive as possible (as found by previous research, e.g. [6]) for the implementation of the intervention [22]. *Immigration background* will be considered during data collection and testing as well as during app development (i.e. it will be ensured that patients and social support providers with an immigration background will also be included in the development as cultural background was found to influence communication behaviors [9, 61, 62, 64]).

This approach will lead to a comprehensive understanding of factors that facilitate and inhibit effective communication and pAE’s. Additionally, it will identify possibilities and potential benefits for the implementation of the intervention in the field, e.g., how communication competences can be integrated into clinical practice beyond the training. Possible options include daily communication logs, regular e-mails with tips on practical application etc.

The results will be used to develop the *training for professionals* (physicians, nursing staff, training assistants, psychologists, midwives), which will be implemented in Stage E of Phase 1 in this project (*pre-experimental study*; see Fig. 4 in the Appendix). The results will also be used to develop the *training for patients and their social support providers* in a *quasi-experimental efficacy study* in Phase 2 (see Fig. 5 in the Appendix). An equivalent procedure applying and testing a training program was successfully performed in a recent study [12]. However, only staff members were addressed and no communication competences or HAPA variables were targeted. In the current study, due to theoretical, ethical and methodological reasons, all individuals should get the benefit of the training. All professionals will be assigned to the intervention group and the evaluation will be done by a pre/post comparison.

#### Translation of the HAPA model into practice – development of the training

The design of the communication training will be informed by theory and previous empirically tested trainings. Exhibiting effective communication will be the desired behavioral outcome as specified in the HAPA model (Fig. 1). Performance modeling, performance desensitization (stemming from work on fears and anxiety disorders), performance exposure and self-instructed performance are all good methods for designing treatments that target enactive mastery experience [37, 38], or maintain the desired behavior in the HAPA model. An example would be to instruct persons to monitor and record how many times a day they have performed effective communication in face of time pressure and to track this on paper (Phase 1 and 2), or in the app (Phase 3). All of the above elements will be integrated into the trainings for professionals (in Phase 1, see Table 4) and for patients and their social support providers (in Phase 2, see Table 5).

**Table 4 Tab4:** Contents and planned structure of the training for professionals (in Phase 1)

*1st part*	*2nd part*
Introduction and warming up; preview learning goals and reflection on expectations	Case studies and analyses with practical exercises and discussion
Training Part 1: Introduction in communication and patient safety	*Module 2*: Improvement of self-efficacy
Training Part 2: Previous experiences with communications skills/challenges	Training Part 3: Further work on communication competences
*Module 1*: Improvements of outcome expectancies and goal setting	*Module 3*: Development and reality check of action and coping plans
Transfer, reflections and feedback	Closing meeting with rounding up, further transfer exercise
Active break with networking and social support

**Table 5 Tab5:** Contents and planned structure of the training for patients and their social support providers (in Phase 2)

*1st day*^*1*^	*2nd day*
Introduction and warming up; preview learning goals and reflection on expectations	Introduction and warming up
Training Part 1: Introduction in communication and patient safety	*Module 2*: Improvement of self-efficacy
Active break for networking and social support	Active morning break
Training Part 2: Previous experiences with communications skills/challenges	Training Part 3: Further work on communication competences
*Module 1*: Improvements of outcome expectancies and goal setting	Active break for networking and social support
Active break for networking and social support mobilization	
Case studies and -analyses with practical exercises and discussion	*Module 3*: Development + reality-check of action and coping plans
Transfer, reflections and feedback	Closing meeting with rounding up further transfer exercise

*Note*: ^1^Patients and their social support providers receive the training during two mornings. If participants are interested in an advanced training, another session will be provided

Training for professionals will take place during work hours and will last approximately 4 hours. Training for patients will last approximately 8 hours. The concrete development of the intervention content and procedure, in addition to the above description, is an important step towards employing *participatory intervention development within this first study phase*. The subsequent publications on the actual intervention contents and procedures will contribute to the current paper and allow for the replication of this study, including the interventions.

